## Abstract

**Background:**

Oral anticoagulation therapy (OAC) is the cornerstone treatment for preventing venous thromboembolism and stroke in patients with nonvalvular atrial fibrillation (NVAF). Despite its significance, challenges in adherence and persistence to OAC regimens have been reported, leading to severe health complications. Central to addressing these challenges is the concept of self-efficacy (SE) in medication management. Currently, there is a noticeable gap in available tools specifically designed to measure SE in OAC self-care management, while such tools are crucial for enhancing patient adherence and overall treatment outcomes.

**Objective:**

This study aims to develop and validate a novel scale aimed to measure self-care self-efficacy (SCSE) in patients with NVAF under OAC, which is the patients’ Self-Care Self-Efficacy Index in Oral Anticoagulation Therapy Management (SCSE-OAC), for English- and Italian-speaking populations. We also seek to assess patients’ SE in managing their OAC treatment effectively and to explore the relationship between SE levels and sociodemographic and clinical variables.

**Methods:**

Using a multiphase, mixed methods observational study design, we first conceptualize the SCSE-OAC through literature reviews, patient focus groups, and expert consensus. The scale’s content validity will be evaluated through patient and expert reviews, while its construct validity is assessed using exploratory and confirmatory factor analyses, ensuring cross-cultural applicability. Criterion validity will be examined through correlations with clinical outcomes. Reliability will be tested via internal consistency and test-retest reliability measures. The study will involve adult outpatients with NVAF on OAC treatment for a minimum of 3 months, using both e-surveys and paper forms for data collection.

**Results:**

It is anticipated that the SCSE-OAC will emerge as a reliable and valid tool for measuring SE in OAC self-care management. It will enable identifying patients at risk of poor adherence due to low SE, facilitating targeted educational interventions. The scale’s validation in both English and Italian-speaking populations will underscore its applicability in diverse clinical settings, contributing significantly to personalized patient-centered care in anticoagulation management.

**Conclusions:**

The development and validation of the SCSE-OAC represent a significant advancement in the field of anticoagulation therapy. Validating the index in English- and Italian-speaking populations will enable personalized patient-centered educational interventions, ultimately improving OAC treatment outcomes. The SCSE-OAC’s focus on SCSE introduces a novel approach to identifying and addressing individual patient needs, promoting adherence, and ultimately improving health outcomes. Future endeavors will seek to extend the validation of the SCSE-OAC across diverse cultural and linguistic landscapes, broadening its applicability in global clinical and research settings. This scale-up effort is crucial for establishing a universal standard for measuring SCSE in OAC management, empowering clinicians and researchers worldwide to tailor effective and culturally sensitive interventions.

**Trial Registration:**

ClinicalTrials.gov NCT05820854; https://tinyurl.com/2mmypey7

**International Registered Report Identifier (IRRID):**

PRR1-10.2196/51489

## Introduction

### Overview

Oral anticoagulation therapy (OAC) represents the primary and secondary prevention choice for venous thromboembolism and stroke in patients with nonvalvular atrial fibrillation (NVAF) [1]. As a life-long treatment, OAC is prescribed for various clinical indications, such as heart failure, congenital heart disease, hematological disorders, and peripheral vascular disease, affecting approximately 2% of the Western population. Despite its efficacy, the quality of anticoagulation control remains a challenge, impacting patient safety, efficacy in preventing thromboembolic events, and overall well-being. With an aging population, OAC use is expected to increase due to the equally increasing prevalence of AF [1].

Research has highlighted patients’ low adherence and persistence to OAC, leading to preventable thromboembolic and hemorrhagic complications like stroke and bleeding. Addressing the underlying health determinants of patient adherence is essential to develop personalized patient-centered educational interventions [2]. Among these determinants, patients’ self-efficacy (SE) plays a crucial role in empowering patients to actively engage in self-care management. SE is associated with patient knowledge and motivation, enabling timely medication intake and self-care activities even under uncertain and challenging conditions [3-5], and will contribute to shared decision-making in OAC treatment [6].

Despite the extensive research on the OAC population, inconsistent results and underreporting of SE persist [3]. One of the main reasons for this inconsistency is the heterogeneity of tools used to measure SE in this specific context. Existing tools, such as the Chronic Disease Self-Efficacy (CDSES) [7], General Self-Efficacy (GSE) [8], and Self-Efficacy for Appropriate Medication Use Scale (SEAMS) [9], have a broad focus and are not tailored to assess the specific SE aspects relevant to OAC self-care management. Consequently, there is a need for a dedicated tool that can capture these challenges and optimize OAC treatment outcomes. In other words, the effects of SE measured using broad tools on specific OAC outcomes might be misleading because the available general tools are not fit to measure aspects of SE that might impact anticoagulation control safety and other OAC-specific results in anticoagulation therapy management, as stated in a recent study [10].

### Self-Care Self-Efficacy Framework

A self-care self-efficacy (SCSE) framework emerges as a valuable theoretical model for developing a measure of OAC-specific SE by being rooted in the middle-range theory of self-care for chronic illness [11,12] and Bandura’s [13] social cognitive theory. In this framework, the SCSE is the patient’s confidence in self-care maintenance (actions to maintain physiological stability), monitoring (efforts to detect signs and symptoms), and management (actions to address functional health behaviors) [14].

The SCSE framework can help researchers and clinicians effectively address OAC-specific challenges related to self-care behaviors in patients undergoing OAC treatment. This approach facilitates the creation of a theory-grounded SE scale that can discern and evaluate complex situations in the context of OAC. These situations involve the behaviors patients need to adhere to maintain physical and mental stability over time (maintenance), monitor signs and symptoms, and implement appropriate actions for symptom management (management) [11,12]. Consequently, the SE within this framework will assess a patient’s confidence in performing these demanding self-care tasks associated with OAC, encompassing decision-making processes, cognitive functioning, and overall health literacy [11,12].

For example, some behaviors investigated within the 3 domains of self-care may reflect how well patients respond to tailored education and preparedness. Other behaviors might address shared challenges in maintaining a healthy status, monitoring changes in the body and mental well-being while on OAC treatment, and making informed decisions in response to unexpected changes. As the project expands, these behaviors could be further tested and integrated into OAC-specific self-care measures. Therefore, developing the Self-Care Self-Efficacy Index in Oral Anticoagulation Therapy Management (SCSE-OAC) aims to offer a comprehensive and nuanced understanding of patients’ SE in managing their OAC treatment effectively by using and incorporating the SCSE framework.

### Aims

This study aims to address the current gap in measuring SE in OAC treatment for NVAF. Existing measurement tools need more specificity and sensitivity to the unique challenges of OAC treatment, as recently highlighted [10]. To address this gap, the primary aim of this research protocol is to outline the design and methodology required to develop the SCSE-OAC in adults with NVAF. The study will provide cross-cultural validity and reliability of the developed measures for both English and Italian-speaking populations.

The secondary aim of this research protocol is to guide analyses to comprehensively describe patients’ SCSE levels in managing OAC for each native-speaking group participating in the study. The data collection rounds designed to validate the SCSE-OAC (primary aim) will lay the groundwork for future investigations into potential associations between patients’ SCSE and their sociodemographic or clinical variables. These findings will be instrumental in tailoring and implementing effective patient-centered educational interventions, ultimately enhancing adherence to OAC treatment and optimizing health outcomes.

## Methods

### Study Design

Following the STROBE (Strengthening the Reporting of Observational studies in Epidemiology) statement, a multiphase, mixed methods observational, and cross-sectional study design will be used. Additionally, the COSMIN (Consensus-based Standards for selecting health status Measurement Instruments) guidelines will be used to evaluate the measurement properties of SCSE-OAC [15].

As depicted in Figure 1, the study will be structured into three main phases (1) conceptualization phase (phase 1), (2) validation phase (phase 2), and (3) reliability phase (phase 3). Phase 1 aims to establish a preliminary item’s pool for the SCSE-OAC and ensure cross-cultural validity for each native-speaking country involved in the research, encompassing both Italian and English versions. The focus of phase 2 is to provide evidence of the internal validity of the SCSE-OAC for each language group. In phase 3, the stability and consistency of the SCSE-OAC over time will be assessed.

**Figure 1 figure1:**
[figure not shown]
Gantt chart of the research activities related to the development and validation of the scale.

### Phase 1: Conceptualization

In this initial phase (conceptualization), the primary objective is to generate a comprehensive list of behaviors that patients should perform in their daily self-care management of OAC. Specifically, we aim to develop a measure of patients’ SCSE, which pertains to their confidence in successfully executing appropriate self-care behaviors to address the unique challenges associated with chronic OAC treatment [16,17]. A total of 3 key substeps will be undertaken to achieve the primary aim of this study, using a mixed methods approach that integrates qualitative and quantitative methodologies to create the first version of the SCSE-OAC.

The first substep entails a systematic scoping literature review, which will help identify existing challenges and issues related to OAC self-care management in adults with NVAF as reported in previous researches. In the second substep, a group of patients with OAC treatment experience will be engaged to validate and potentially modify the initial set of behaviors identified in the literature review [18]. Similarly, in the third substep, input from health care experts with expertise in OAC management will be sought to further validate and refine the list of challenges or issues. Subsequently, the provisional version of the SCSE-OAC will be subject to cross-translation and cultural adaptation to ensure its relevance and applicability in the validation phase (phase 2) of the study.

More precisely, the systematic scoping literature review will be performed through the main academic research databases (PubMed, CINHAL, Scopus, and Web of Science) to identify the key pool of patients’ challenging behaviors in OAC management. In this stage, the “Population, Concept, Context” (PCC) framework will be used to develop the queries for each database [19,20] and be consistent with the framework to conduct scoping reviews [21].

In the second substep of this phase, purposive sampling of adult outpatients (18 years of age or older) with NVAF treated in OAC for at least 3 months will be involved in a small focus-group discussion to share the most relevant challenges they lived or perceived in the self-care management of OAC. In the methodology for our focus group discussions, we have chosen to start with a base number of 5 participants. This decision is grounded in qualitative research practices where smaller groups could facilitate more in-depth discussions, allowing each participant ample opportunity to share their experiences and insights [22]. This size is considered sufficient to begin exploring the range of patient perspectives on managing OAC, particularly given the specialized nature of the topic and the targeted patient population [22]. However, recognizing the importance of achieving comprehensive data saturation, our approach is designed to be flexible and iterative. After the initial focus group with 5 participants, we will continuously assess the information gathered for new and recurring themes. If additional perspectives are needed to achieve saturation—where no new information is observed in the data—we will conduct subsequent rounds of focus groups, incorporating more participants as required. This iterative process ensures that our research captures a full spectrum of patient experiences and challenges related to self-care management of OAC, thus enhancing the validity and applicability of our findings [23]. Therefore, a group of voluntary patients will be identified for each country involved in the study (Italy and Australia). A bilingual-trained moderator will be identified to guide the discussion for each patient group. Finally, a list of OAC challenges by patients’ views will be integrated with the literature review results, and the advice from the interviewed patients will contribute to defining the items’ wording. This phase is anticipated to end in October 2024.

After the patients’ focus-group discussion, a panel of experts (ie, physician, nurse, and pharmacist) will assess the relevance of each OAC-specific required behavior (item) identified in the previous phases. A multidisciplinary group of bilingual health care professionals with a minimum of 1 year of clinical experience in OAC management will be asked to rate the relevance of each item (ie, OAC challenges) on a 4-point Likert scale (1: completely disagree and 4: completely agree). Therefore, an overall interrater agreement among experts will be assessed through the Fleiss kappa index, and a value of more than 0.40 might be acceptable in a sample size ranging from 6 to 50 experts. Any divergence will be solved with consensus discussion.

In the last substep of phase 1, the provisional English version of the SCSE-OAC will be in parallel translated and cross-culturally adapted for each native-speaking country involved in the study (ie, Italian). Therefore, an independent group of bilingual experts will be involved in an iterative forward-backward translation process to ensure that the final version of the scale will be conceptually and linguistically correct and understandable to people of all levels of education by being culturally acceptable. Brislin’s translation procedure will be followed [24]. More specifically, 2 expert bilinguals who are native speakers of the target language will translate the English version of the SCSE-OAC into the Italian language, and a third expert will review the 2 translations to achieve the best possible reconciled translation. After that, another 2 bilingual experts who are native speakers of the target language with fluency in English will be involved in the back-translation of the previously reconciled translation to the original language (ie, Italian back to the English language). The results of all 3 tasks (translation, reconciliation, and back-translation) should be forwarded to a permanent panel of experts or translation coordinator to review the process. As a result of the translation process, 2 translated versions of SCSE-OAC will be available (1) SCSE-OAC for the Italian-speaking patients’ group and (2) SCSE-OAC for English-speaking patients’ group. At the end of this translation process, a pilot test will be performed to assess the readability and comprehensibility of the items for each native-speaking group (10-15 patients). Therefore, each patient group will be asked to fulfill the preliminary translated version of SCSE-OAC and highlight any items that are not clear to them. All comments and suggestions will be taken into account. This phase is anticipated to end in December 2024.

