### Phase 2: Validation

This second phase (ie, validation phase) aims to define the construct intended to be measured, providing evidence of psychometrics validity for each translated version of SCSE-OAC. Two main substeps will be performed (1) content and face validity and (2) construct validity.

According to the COSMIN guideline, the content validity of the scale will be assessed based on the key criteria of relevance, comprehensiveness, and comprehensibility. In other words, each item will be analyzed by patients and health care professionals for content, meaning, wording, and format. As per the relevance criteria, we will ask to judge the items’ relevance for the construct of interest (ie, SCSE) on a 4-point Likert scale (1=not relevant, 2=somewhat relevant, 3=quite relevant, and 4=highly relevant), with the following question

Please evaluate the relevance of the following self-care behaviors in managing your oral anticoagulation medication. Which behaviors do you find relevant to your daily life with OAC treatment?

Content validity index (CVI) will be computed at the item and overall scale (ie, I-CVIs and S-CVI), considering a critical threshold value equal to 0.70 for I-CVIs and 0.80 for S-CVI. For each native-speaking country, a minimum of 15 patients will be enrolled to participate in the study.

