### Data Analysis

The relevant number of factors to be retained in EFA data analysis will be done on the parameters of scree-test, parallel analysis, and factor rotation. More specifically, in the parallel analysis, if the eigenvalue of the original data’s factor is greater than the average of the eigenvalues of the parallel factor, that factor is retained. Likewise, the item retention will be assessed using factor loadings evaluations, where items with loadings >.40 will be retained. The structural model derived from EFA has to be used for both language groups in the CFA data analysis. The goodness of each model fit will be assessed based on the indexes of root-mean-square error of approximation (RMSEA; <.01) “excellent fit;” (<.05) “good fit;” (<.08) “mediocre fit;” comparative fit index (CFI) and Tucker-Lewis Index (TLI; >.90) and (>.95) [17,18]; SRMR (<.08) [19]; and chi-square test [25]. Furthermore, the multivariate normality of each model will be checked with the Mardia test, supposing that the multivariate skewness and kurtosis are significant. In the case of normality violation, a robust maximum likelihood estimator will be used.

After estimating the baseline model of scale for each language group, we will perform the Multi-Group Confirmatory Factor Analysis (MGCFA) to assess the cross-cultural validity. In other words, we will assess if the configural, metric, and scalar structure of SCSE-OAM is equivalent across 2 different language groups (English vs the Italian language). Achieving multi-group equivalence is pivotal to generating meaningful cross-group comparisons. Testing the measurement invariance means following a series of iterative analytical steps that bring from the largest model (where each language group has its parameters) to the more restricted one (where all the parameters are equal across the language group). This process stops when the model comparison is significant (ie, the large model fits the data significantly better than the more restricted one). A chi-square difference test will be performed to compare each model with the previous one to check whether a stronger invariance assumption holds. Data analysis will be performed in MPlus (Muthén & Muthén; version 8.1).

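### The Italian-to-English back-translation is assigned to native Italian speakers, which weakens the only described check of the Italian items against the English source

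*Protocol article*

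**What the plan says.** The last substep of Phase 1 (Methods, Phase 1: Conceptualization) starts from a provisional English scale and produces an Italian one. For the forward step, "2 expert bilinguals who are native speakers of the target language will translate the English version of the SCSE-OAC into the Italian language". One further expert then reconciles the two translations. For the back step, "another 2 bilingual experts who are native speakers of the target language with fluency in English will be involved in the back-translation", and the direction is given as "to the original language (ie, Italian back to the English language").

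The article names the Brislin method by citation only: "translation procedure will be followed [24]".

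Several checks follow:
- The results of translation, reconciliation and back-translation "should be forwarded to a permanent panel of experts or translation coordinator to review the process".
- After translation, "a pilot test will be performed to assess the readability and comprehensibility of the items for each native-speaking group (10-15 patients"), and patients mark items that are unclear to them.
- In Phase 2: Validation, "each item will be analyzed by patients and health care professionals for content, meaning, wording, and format". This round has at least 15 patients per country, 10 professionals and an open question on comprehensiveness and comprehensibility.

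Factor analysis comes after these steps. The Data Analysis section then tests whether the "configural, metric, and scalar structure of SCSE-OAM is equivalent across 2 different language groups".

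**The concern.** In the forward step the translators are native in the language they write. In the back step they are not: the text produced is English and its authors are native speakers of Italian.

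The back-translation serves to show, in English, what the Italian items say, so that they can be held against the source. If the English is written by non-native speakers, a discrepancy has two possible causes: the Italian item has drifted, or the English rendering is imperfect. A real fault may be excused as awkward English, and a sound item may be altered for no reason.

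Cross-cultural validity in both languages is part of the primary aim. If a meaning shift does survive to the multi-group analysis, that analysis can show that an item behaves differently in the two groups. It cannot by itself separate a translation error from a cultural difference.

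**Working it through.** No figure in the plan bears on this point, so there is nothing to recompute. The check is a reading of the text in three steps.

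**Step 1: which language is the target language?** The forward-translation sentence has native speakers of the target language turning English into Italian. Target language therefore means Italian, and the English version is the original. The back-translation sentence confirms this by describing the return from Italian to English as a return to the original language.

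**Step 2: who back-translates?** The same term is used for the back-translators, with fluency in English added. That addition would be redundant for native English speakers. The natural reading is native Italian speakers.

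| Step | Language written | Stated native language of those writing |
|---|---|---|
| Forward translation (2 experts) | Italian | Italian |
| Reconciliation (1 expert) | Italian | not stated |
| Back-translation (2 other experts) | English | Italian |
| Panel or coordinator review | none; reviews the three outputs | not stated |

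No row requires a native English speaker.

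**Step 3: which other step compares Italian meaning with the English source before the main data collection?**

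- *Expert relevance rating (Phase 1).* The raters are bilingual, but they rate the items before translation, so they do not see the Italian version.
- *Panel or coordinator review.* It sees all three outputs, but its evidence on equivalence is this same back-translation.
- *Pilot, 10-15 patients per language group.* Patients read the version in their own language and mark what is unclear. An Italian item that reads well but means something slightly different gives them no reason to object.
- *Content and face validity.* Patients and professionals judge relevance, wording, coverage and clarity. Nothing says that they see both versions, and these professionals are not described as bilingual.

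Back-translation is thus the only described step that sets the Italian meaning against the source. The later rounds can catch unclear or unnatural Italian. A clear item with a shifted meaning could pass them.

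**The case against.** The strongest case on the other side has four parts.

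**The process has several layers.** It is described as iterative, with reconciliation, panel or coordinator review, a pilot whose comments will all be considered, and a content-validity round with numerical thresholds before any factor analysis. This stands as a reason to speak of raised risk only. A reader might infer that faulty items will reach the cross-language analysis. The document does not support that, because these checks lie in between and some faults would be caught.

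**Literal translation is not specific to this assignment.** A reader might infer that native Italian speakers in particular would let word-for-word Italian through, by restoring the intended English. That does not follow. Literal Italian can return to near-source English whoever back-translates it, native Italian speakers may be better placed to notice that it is unnatural, and Italian patients in the pilot can flag it. What is specific to this assignment is the doubt about the English. It is true that an odd back-translation is at least visible to the panel, but the panel still has to decide what caused it.

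**The wording may be loose.** The same paragraph counts the English original as one of two translated versions, so target language might have been meant as English in the back step. The added phrase on English fluency makes this unlikely. If it was meant, the sentence is wrong as printed and needs the same edit.

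**Details may sit in the full protocol or the cited method.** This stands for whether the back-translators are kept unaware of the source, and no fault is found there. Nor can a departure from the cited procedure be claimed, since that source is not at hand. The back-translators' native language, however, is stated, so that part is a choice and not an omission.

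**Conclusion.** The point holds in limited form. As written, the plan gives the English back-translation to native Italian speakers and requires no native English speaker in the translation process. This makes discrepancies harder to interpret at the one described step that tests equivalence of meaning, and puts more weight on a panel or coordinator working from the same text. The later rounds reduce the risk of a mistranslated item reaching the invariance analysis but do not remove it.

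The size cannot be derived from the document. With the hypothesised 10 items, one item is 1/10 = 10% of the scale, but what a faulty item would do to invariance depends on how far its meaning has shifted, which is unknown. A reader might infer that one such item is enough to break metric or scalar invariance, or that an item found faulty after data collection could only be dropped. The document contains no calculation or rule that supports either.

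The conclusion rests on reading target language as Italian in both sentences, and on the patient and professional rounds using a single language version each, since no comparison of versions is described.

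**What to change.** In the last substep of Phase 1, amend the back-translation sentence so that the 2 back-translators are native English speakers fluent in Italian who have not seen the English source version. Keep the number of translators, the reconciliation and the panel or coordinator review as they are. If native Italian back-translators are intended, state the reason.

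The cost is small: the headcount does not change, and the Australian part of the study is a plausible place to recruit. The downside is that native English speakers fluent in Italian are slightly harder to find. The change is cheapest before the main data collection; afterwards, a faulty Italian item could not be put right in the data already collected.
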